### Objectives

The research objective is to examine the therapeutic effects of rTMS on cognitive function in veterans with PD-MCI. The central hypothesis is that rTMS will safely improve cognitive function in PD-MCI.

There are 2 aims of the study. Aim 1 is to determine the safety and feasibility of rTMS treatment. The hypothesis is that 10 high-frequency rTMS sessions will be (1) safe, as evidenced by the lack of difference in the number of research-related adverse events experienced by the active rTMS group compared to the sham rTMS group; and (2) feasible, as indicated by participant protocol completion rates.

Aim 2 is to determine the behavioral effects of rTMS treatment. A battery of neuropsychological tests will be administered at baseline, end point (after the 10th rTMS session), and the 1-month follow-up. The hypothesis is that active rTMS, compared to sham rTMS, will enhance cognitive test performance after rTMS completion and at the 1-month follow-up. The primary outcome will be change in executive function (ie, end point minus baseline) as measured using the National Institutes of Health–sponsored Executive Abilities: Measures and Instruments for Neurobehavioral Evaluation and Research (NIH-EXAMINER) Executive Composite score.

To address the study objectives, a prospective parallel-group RCT will be conducted. A convenience sample of veterans (N=66) who have been screened and diagnosed with PD-MCI will be randomly assigned to 1 of 2 groups: active rTMS or sham rTMS to the left DLPFC.

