Taking all this into consideration, as well as the fact that this is a small-scale trial, the effect size of 0.48 found in the aforementioned meta-analysis [55] was estimated for this RCT. The sample size was determined using a 2-level mixed-effects longitudinal model with random participant intercept and random participant slope. The end point effect size was fixed at 0.48, which is considered moderate. The participant intercept and slope variances were fixed at 2.3 and 0.3, respectively. In addition, the error variance was fixed at 2.0, which should be considered moderate. Using this combination of parameters, we determined that a sample size of 71 per group (active and sham) considering an attrition rate of 10% will be needed to achieve 80% power while maintaining the type 1 error rate at 5%. The RMASS software was used for this power analysis [56]. Hence, a total of 156 participants will be recruited for this proposed study.

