#### Data Management Methods: Statistical Methods

For safety outcomes, the Poisson distribution for the number of research-related adverse events will be fitted for each treatment group. Negative binomial distributions will be used in case overdispersion is present. The mean parameters (λ) of these 2 distributions will be tested to see whether any difference in the average number of adverse events in each treatment group exists. Lack of significance will suggest that active rTMS is as safe as sham rTMS in terms of adverse events. To further compare the trend in adverse events between the 2 groups, we will use a 3-level mixed-effects Poisson regression model, and the group-by-time interaction parameter will be tested to examine whether active rTMS has more adverse events than sham rTMS over time.

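### Aim 1 reads a non-significant adverse-event comparison as evidence that active rTMS is as safe as sham, with no margin and no sizing for safety; the interaction test is also misdescribed

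*Protocol article*

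**What the plan says.** In Objectives, the first part of the Aim 1 hypothesis is that the treatment will be "safe, as evidenced by the lack of difference in the number of research-related adverse events experienced by the active rTMS group" compared with sham. Hypothesized Principal Findings repeats this.

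The safety paragraph of Data Management Methods: Statistical Methods puts it into practice in two steps.

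- First, "the Poisson distribution for the number of research-related adverse events will be fitted for each treatment group", with a negative binomial alternative for overdispersion. Then: "The mean parameters (λ) of these 2 distributions will be tested to see whether any difference in the average number of adverse events" exists between the groups. The reading rule follows: "Lack of significance will suggest that active rTMS is as safe as sham rTMS in terms of adverse events".
- Second, to compare trends, a 3-level mixed-effects Poisson model is fitted, and "the group-by-time interaction parameter will be tested to examine whether active rTMS has more adverse events than sham rTMS over time".

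Sample Size Determination concerns the cognitive outcome only: "The end point effect size was fixed at 0.48", and "a sample size of 71 per group (active and sham) considering an attrition rate of 10% will be needed to achieve 80% power". It then gives a recruitment total of 156, whereas Objectives gives N=66. No margin, confidence-limit criterion, power or expected event rate is stated for safety.

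**The concern.** A test of difference puts the burden of proof on showing harm. If the trial is small, events are few or counts are overdispersed, the test will often be non-significant whatever the truth. Under the stated rule, that outcome counts in favour of safety, so less information makes the reassuring reading more likely.

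The second step has a different fault. A group-by-time interaction asks whether the arms diverge over time, whereas the text says it examines whether active has more events. A reader of the eventual report could take a null interaction as further reassurance about the overall rate, which it would not be.

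Safety is the trial's first aim, under an investigational device exemption. The article's Background says there may be unknown risks and that reporting adverse events will help fill gaps in the safety literature for this population. A statement that active is as safe as sham, resting only on a non-significant test, would enter that literature with more weight than the data carry.

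**Working it through.** **1. What the stated sample size covers.** The inputs are all from Sample Size Determination: effect 0.48, intercept variance 2.3, slope variance 0.3, error variance 2.0, 80% power, 5% type 1 error and 10% attrition. Assume times coded 0, 1, 2 and the effect expressed in SDs at the last time.

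- SD at the last time = √(2.3 + 4×0.3 + 2.0) = √5.5 = 2.345
- Slope difference = 0.48 × 2.345 / 2 = 0.563
- Variance of one participant's slope = 0.3 + 2.0/2 = 1.3
- n per arm = 2 × 1.3 × (1.960 + 0.842)² / 0.563² = 64.4, and 64.4/0.9 = 71.6

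This is within 1% of the stated 71. No adverse-event quantity enters the calculation, so the 80% power says nothing about the safety comparison.

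**2. Chance that the test of means misses a true excess.** The inputs are:

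- n = 33 per arm (66/2, Objectives) and n = 78 per arm (156/2, Sample Size Determination), taking equal allocation
- two-sided 5% level, assumed because the article states 5% only for efficacy
- sham mean λ = 0.5 to 1.0 events per participant, assumed
- dispersion k = 0 (Poisson) or 0.5 (negative binomial), assumed

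For a true rate ratio RR, the test on the log scale has

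SE = √[1/(nλ) + 1/(nλRR) + 2k/n], z = ln(RR)/SE, chance of missing ≈ 1 − Φ(z − 1.96).

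Example: n = 33, λ = 0.5, RR = 1.5, k = 0 gives SE = √(1/16.5 + 1/24.75) = 0.318 and z = 0.405/0.318 = 1.28. The test misses about 75% of the time.

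| True RR | n per arm | Poisson, λ=0.5 | Poisson, λ=1.0 | k=0.5, λ=0.5 | k=0.5, λ=1.0 |
|---|---|---|---|---|---|
| 1.5 | 33 | 75% | 56% | 80% | 70% |
| 1.5 | 78 | 50% | 21% | 59% | 41% |
| 2.0 | 33 | 37% | 10% | 49% | 29% |
| 2.0 | 78 | 6% | 0.1% | 14% | 3% |

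An enumeration of the Poisson score test agrees closely. For a doubling it misses 34% (λ=0.5) and 8% (λ=1.0) at 33 per arm, and 5% and 0.1% at 78.

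**3. What a perfectly null result would exclude.** If the observed rates are equal, the upper 95% limit of the rate ratio under Poisson is exp(1.96 × √(2/(nλ))).

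- n = 33: 1.98 at λ = 0.5, 1.62 at λ = 1.0
- n = 78: 1.56 at λ = 0.5, 1.37 at λ = 1.0

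Even identical observed rates would therefore leave an excess of about 60-100% unexcluded at N=66, and about 40-60% at N=156.

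**4. The interaction.** With a log link, let the sham log rate at time t be a + f(t). If active has a constant rate ratio, its log rate is a + f(t) + ln(RR). The difference is ln(RR) at every t, so the group-by-time term is zero whatever the size of RR.

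A simulation gives the same result (10 sessions, participant heterogeneity with SD 0.7 on the log scale, 1,000 runs per setting). Under constant rate ratios of 1.5, 2 and 3, the interaction test rejected in 3.6-6.1% of runs, about its type 1 error. At a ratio of 3, the test of means rejected in 91.5-100%.

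**The case against.** The strongest reply is that a constant excess is what the first safety test targets. The interaction is introduced as a further comparison of trends, and no conclusion of equal safety is attached to it. This stands. A reader might infer that the interaction's blindness to a constant excess is what would let a harmful arm pass as safe, but the article does not support that. A false reassurance would come from low power of the test of means. The fault in the interaction is its description. Even that assumes time covers the treatment period. The article defines neither time nor the three levels, and a pre-treatment time point could let the interaction pick up part of an excess.

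A second reply is that the larger sample size softens the problem. This also stands in part. At 78 per arm with Poisson counts in the assumed range, a doubling would rarely be missed. A 50% excess still would be, in about 21-50% of trials.

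A third reply is that the rule is worded as suggestive and confined to adverse events. No stopping rule or primary-outcome decision is tied to it. A medical monitor, before-and-after checks at each session and a log of all events operate independently of it. These points bear on severity. They do not rescue the inference, because Objectives makes absence of a difference the evidence for the Aim 1 safety hypothesis.

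A separate analysis plan may exist, but it would not make a rule that the article itself states a sound one.

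**Conclusion.** The concern holds in two limited parts.

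First, the rule that reads non-significance as comparable safety is unsound as written, and nothing in the stated design compensates for it. Its practical size depends on event rates that the article does not give. Over 0.5-1.0 events per sham participant with Poisson counts, a 50% excess would be missed about 56-75% of the time at N=66 and 21-50% at N=156. A doubling would be missed about 10-37% and 0.1-6%. Lower rates or overdispersion make this worse, and higher Poisson rates make it better. Which end applies also depends on which total holds; the conflict between 66 and 156 is a separate matter.

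Second, the interaction is described as answering a question about excess that it does not answer if time runs over the treatment period.

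It would go too far to say that the plan has no test able to find a constant excess, or that a harmful arm would usually pass. This should be fixed before unblinding, but it does not invalidate the trial or its safety monitoring.

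**What to change.** - **Rule.** Delete the sentence that takes lack of significance as suggesting equal safety, and reword the Aim 1 hypothesis in Objectives and in Hypothesized Principal Findings to match.
- **Reporting.** Give the active/sham rate ratio and the rate difference with 95% confidence intervals from the Poisson or negative binomial model already planned.
- **Claim.** Conclude that active is no worse than sham only if the upper limit lies below a margin that the sponsor fixes before unblinding. Otherwise, state which excess cannot be ruled out and call the result inconclusive.
- **Interaction.** Describe it as a comparison of time patterns only. Take the average excess from the comparison of means, or from a group effect in a model without the interaction. If the interaction is kept, centre time; otherwise the group coefficient is the ratio at time zero.

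No new data are needed. The wording change goes through the amendment approval described under Human Subject Ethics Approval.

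The real cost is that the safety result will often be inconclusive, especially at N=66. For illustration only, since the article gives no margin, take one-sided 2.5%, 80% power and a true ratio of 1. With Poisson counts, n per arm = (2/λ) × (1.960 + 0.842)² / (ln margin)². A margin of 2.0 needs 66 per arm at 0.5 events per participant and 33 at 1.0. A margin of 1.5 needs 191 and 96. Overdispersion raises these numbers. If the sponsor does not wish to set a margin, safety can be reported descriptively with intervals and no claim of comparability.

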**Results:**

Safety will be assessed using the number of research-related adverse events experienced by the active rTMS group compared to the sham rTMS group. Feasibility will be assessed using protocol completion rates. To examine preliminary effects of rTMS, participants will complete a standardized neurocognitive battery assessment at baseline, end point, and 1-month follow-up. The primary study outcome is the change in score from baseline to end point on the National Institutes of Health–sponsored Executive Abilities: Measures and Instruments for Neurobehavioral Evaluation and Research Executive Composite score. This project was funded in June 2019, with additional funding secured in April 2024. As of April 2025, a total of 18 veterans with PD-MCI have completed the randomized controlled trial phase. Data collection is ongoing and will be completed by March 2027. We expect the results of this study to be available by March 2028.

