There is considerable evidence that rTMS performed in compliance with the recommended safety guidelines [19-21] is reasonably safe with mild side effects. The most serious risk of rTMS is seizures; however, the risk of seizure in healthy persons is exceedingly low [22]. A safety review indicates no reported rTMS-induced seizures in the PD population and that the more common safety issues related to rTMS in PD are similar to those in the non-PD population [23]. The most common side effects include a mild transient headache, scalp pain at the stimulation site, neck pain, tooth pain, transient changes in audition, and syncope. While rTMS is considered a safe procedure when provided within safety guidelines, it is important to remember that it is an experimental treatment in PD without Food and Drug Administration (FDA) clearance. Thus, there may be unknown risks. Safety is of the highest priority; thus, it is critical that investigators measure and report on the presence or absence of adverse events [19]—this will help address existing gaps in the PD rTMS safety literature.

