## Discussion

### Hypothesized Principal Findings

The overall research objective is to examine the therapeutic effects of rTMS on cognitive function in veterans with PD-MCI. The central hypothesis is that rTMS will safely improve cognitive function in PD-MCI. The first aim of the study is to determine the safety and feasibility of rTMS treatment. The hypothesis is that 10 high-frequency rTMS sessions will be (1) safe, as evidenced by the lack of difference in the number of research-related adverse events experienced by the active rTMS group compared to the sham rTMS group; and (2) feasible, as indicated by participant protocol completion rates. The second aim of the study is to determine the behavioral effects of rTMS. The hypothesis is that active rTMS, compared to sham rTMS, will enhance cognitive test performance after rTMS completion and at the 1-month follow-up.

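### A non-significant difference in adverse event counts is read as active rTMS being as safe as sham, with no margin, interval or safety power to support it

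*Protocol article*

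**What the plan says.** In the Protocol article, under Data Management Methods: Statistical Methods, "the Poisson distribution for the number of research-related adverse events will be fitted for each treatment group", with a negative binomial alternative if there is overdispersion. The two means are tested for any difference, and the reading of a null result is fixed in advance: "Lack of significance will suggest that active rTMS is as safe as sham rTMS in terms of adverse events".

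A second, mixed-effects Poisson model tests the group-by-time interaction to see "whether active rTMS has more adverse events than sham rTMS over time". It has no seriousness or severity term.

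The same criterion appears at the level of the aims. Under Objectives, Aim 1 expects treatment to be "safe, as evidenced by the lack of difference in the number of research-related adverse events experienced by the active rTMS group", and Hypothesized Principal Findings repeats this. The Results paragraph of the abstract names the same measure: "Safety will be assessed using the number of research-related adverse events experienced by the active rTMS group compared to the sham rTMS group".

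Background and Rationale describes harms of very different weight. On one side, "The most serious risk of rTMS is seizures"; on the other, "The most common side effects include a mild transient headache, scalp pain at the stimulation site, neck pain, tooth pain". Harms: Safety Monitoring says that serious and nonserious events are both logged and that a monitoring sheet carries a severity scale. Neither enters the stated safety reading.

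**The concern.** A test that fails to find a difference does not show that there is none. To support a claim of being as safe, one needs a margin that the interval must exclude, or at least an interval showing which excess the data still allow. The article gives neither. Its only power statement, under Sample Size Determination, concerns the cognitive endpoint. Under the stated rule, the fewer events there are and the smaller the trial is, the easier it becomes to reach the favourable reading.

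The rule also gives a headache and a seizure equal weight, although seriousness is on record for each event.

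Safety is half of Aim 1, and the article calls it the highest priority for a use of the device that lacks FDA clearance. The abstract says that the results will set the stage for future research, so an unsupported statement of equal safety would be carried into later work.

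**Working it through.** **The plan's own figures.** There is none to reproduce for safety: no event rate, margin, interval criterion or power. The only inputs are the arm sizes: 33 per arm from N=66 (Objectives, assuming equal allocation) and 71 per arm (Sample Size Determination). The event counts below are therefore assumed, for illustration.

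**Step 1: what equal counts leave open.** Let a and b be the event counts in active and sham, with equal arms, equal follow-up and independent Poisson counts. Given the total a+b, a is binomial with probability p = RR/(1+RR), where RR is the active-to-sham rate ratio. Take exact (Clopper-Pearson) 95% limits for p and convert them by RR = p/(1−p).

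| Events, active vs sham | 95% limits for p | 95% CI for rate ratio |
|---|---|---|
| 33 vs 33 (one per participant at N=66) | 0.374 to 0.626 | 0.374/0.626 = 0.60 to 0.626/0.374 = 1.67 |
| 71 vs 71 (one per participant at 71 per arm) | 0.415 to 0.585 | 0.71 to 1.41 |
| 3 vs 3 | 0.118 to 0.882 | 0.13 to 7.5 |

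In every row the observed difference is zero, the most favourable result for the rule short of fewer events in active. Even so, the data do not exclude an excess of 41% (71 vs 71), 67% (33 vs 33) or more than sevenfold (3 vs 3). The rule returns the same reading for all three. Overdispersion, which the plan allows for, would widen these intervals.

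**Step 2: a small excess of serious events.** Suppose two serious related events in active, none in sham, and no other events.
- z test: z = (a−b)/√(a+b) = 2/√2 = 1.41, two-sided p = 0.16.
- Exact test: p = 2 × 0.5² = 0.50.

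Both are non-significant, so the stated reading applies. No assumption about mild events is needed. Equal numbers of mild events in both arms would only reduce z further, because they add to the denominator and not to the numerator.

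**Step 3: whether a test on serious events alone would repair this.** By the exact test, 5 vs 0 gives p = 2 × 0.5⁵ = 0.0625 and 6 vs 0 gives p = 2 × 0.5⁶ = 0.031. Five serious events against none would still be non-significant. The remedy is therefore estimation, not another significance test.

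**The case against.** **The wording is hedged.** It says that non-significance will suggest equal safety, and only in terms of adverse events. It is not a stopping rule, and a medical monitor is consulted during the trial. That is true, and participants do not depend on this p-value for protection. But monitoring does not repair the final inference, and Aim 1 states the same lack of difference as evidence of safety.

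**More safety outcomes may be planned.** The methods section opens its safety paragraph in the plural and later says that the modelling will be reported for each outcome of interest. A full protocol or analysis plan may contain tables by seriousness and severity. This stands: the absence of such tables from a journal article is no fault. The point concerns the inference that the article does state.

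**The total count might hide many serious events.** A reader might infer this, but the documents do not support a size for it. By the z test at 33 per arm, the extra active-arm events needed for significance run from 4 with no mild events to 25 with two per participant in each arm. The article gives no mild-event rate. It also names side effects and adverse events separately and does not reproduce the logging criteria, so it is unknown whether mild symptoms enter the count. If mild events were more frequent under active treatment, the total count could detect the difference. For example, assume one mild event per sham participant, 1.3 times as many in active, and worse events at 0.20 vs 0.02 per participant. At 71 per arm, power would then be 72%.

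**Serious-event intervals will be very wide.** This is correct: 7 vs 1 events gives a rate ratio interval of 0.9 to 315. That is a reason to show the uncertainty, not to replace it with a non-significant p-value.

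**Conclusion.** The concern holds as a fault of inference. The plan fixes in advance that non-significance on the count of related adverse events suggests equal safety, and nothing stated in the article licenses that step. Exactly equal counts still leave upper rate-ratio limits of 1.41 to 7.5 in the cases shown, and 2 vs 0 serious events passes the rule. These results assume equal arms, Poisson counts and the illustrative event numbers. The logical point needs none of them.

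A secondary point also holds, without a size: seriousness is logged but has no part in the stated reading. It would go too far to say that the plan disregards serious events, or that the count will mask a particular excess of them. Neither follows from the article.

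**What to change.** Under Data Management Methods: Statistical Methods, delete the sentence on lack of significance and replace it with:

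1. the active-to-sham rate ratio of research-related adverse events with its 95% confidence interval, from the Poisson model or, if there is overdispersion, the negative binomial model;
2. serious related events by arm, with exact 95% confidence intervals;
3. any seizure or syncope listed as individual cases, without a test.

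Base the Aim 1 safety statement on these estimates and intervals together, and align the wording in the abstract, Objectives and Hypothesized Principal Findings. A separate stratum of higher-severity events is optional. The article does not show that its severity scale grades logged events, so that stratum would need a grading rule and blinded grading.

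**Cost.** Wording and a short table. Seriousness is already logged, and data collection runs to March 2027, so no new data are needed. The drawback is wide intervals, above all for serious events at N=66, and therefore a less favourable safety statement than the present rule would allow.

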#### Outcomes

The primary study outcome is the change in score from baseline to end point on the NIH-EXAMINER Executive Composite score. The composite score is advantageous because it combines performance across various aspects of executive function consistently reported to be impacted by PD [36]. It is derived using item response theory, which can improve sensitivity and increase statistical power over standard scoring methods [37]. Seven tests in the NIH-EXAMINER will be used to compute the composite score, as detailed in Table 2. This battery takes approximately 30 minutes to administer, and each test has 3 alternate forms to help avoid practice or learning effects when administered multiple times during the study.

**Table 2 table2:** Study assessments^a^.

Assessment name		Construct measure

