### Assignment of Interventions

Participants will be randomized to either the active or sham rTMS. The sequence will be produced by the study biostatistician using an online random number generator. There will be no stratification. An unblinded study team member will assign the participant number series codes from the MagVenture study master edition. These participant codes correspond to randomized treatment numbers that are entered into the MagVenture MagProX100 stimulator before each treatment session.

Participants and study team members administering and scoring outcome measures, as well as the study biostatistician, will be blinded to group assignment. Researchers blinded to treatment group will administer outcome measurements. The effectiveness of blinding will be evaluated using data collected from end point questionnaires that assess perception of the intervention.

Unblinding will occur after participants have completed the study.

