For neuropsychological outcomes, all data will be analyzed using a 2-level longitudinal mixed-effects model with random participant effects to incorporate correlation of measurements nested within the same participant. The model will also include covariates such as medication dose and anxiety and depression levels. Parameters will be estimated using measurements from all 3 time points (ie, baseline, end point, and follow-up). The group-by-time interaction parameter will be used to examine the difference in the trends of the active rTMS group compared to the sham rTMS group. The significance of this parameter will indicate whether treatment is efficacious in terms of executive function over time when adjusted for the identified covariates. To assess the immediate effects of rTMS, one contrast using means of test scores at baseline and end point from the experimental group will be obtained, and the other contrast will be obtained from those same types of means for the control group. These 2 contrasts will then be tested using a 2-tailed *t* test to compare the change scores of the 2 groups. To assess sustainability of the rTMS effects, contrasts using means of test scores at end point and follow-up will be obtained for each group, and the contrast will then be compared using a *t* test. Estimates of variance components from mixed-model analysis will be used to calculate test statistics. To account for the many-to-many comparisons of secondary outcomes, we will use a multivariate mixed-effects model with the aforementioned covariates. For every secondary outcome component, there will be fixed as well as random components. The random component will address the within-subject correlation and the heterogeneity between multiple outcomes. Every component will have its own trend, which means that the recovery curve may be outcome specific. The group-by-time interaction parameter of each secondary outcome will be tested to examine whether cognitive function in the active rTMS group is different from that in the sham rTMS group. The false discovery rate will be addressed using Benjamini and Hochberg [57] procedures, with a false discovery rate level of 0.05. Data analysis will be performed using the SAS PROC MIXED statement (version 9.3; SAS Institute). This modeling process will be reported for each outcome of interest for the safety and neuropsychological assessments. Every effort will be made to avoid missing data; we will try to understand the missingness pattern and why and how the missingness occurred. No missing value imputation technique will be used if Little test supports that data are missing completely at random. Otherwise, proper missing data imputation techniques (eg, imputation with mean, nearest neighbor, or last observation carried forward) will be used.

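### The end-point comparison of group change scores is valid but does not adjust for baseline Executive Composite, so it loses precision that data already collected could supply

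*Protocol article*

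**What the plan says.** - **Outcome** (Outcomes): "The primary study outcome is the change in score from baseline to end point on the NIH-EXAMINER Executive Composite score".
- **Contrast** (Data Management Methods: Statistical Methods): "one contrast using means of test scores at baseline and end point from the experimental group will be obtained", with a matching contrast for the control group. The two contrasts then go into a 2-tailed t test "to compare the change scores of the 2 groups". Each group's own baseline mean therefore enters its contrast.
- **Role of baseline** (same section): it is one of three response measurements. "Parameters will be estimated using measurements from all 3 time points (ie, baseline, end point, and follow-up").
- **Covariates** (same section): "The model will also include covariates such as medication dose and anxiety and depression levels". Baseline Executive Composite is not named.
- **Second efficacy test** (same section): the group-by-time interaction over the three visits is also described as showing whether treatment works.
- **Planning variances** (Sample Size Determination): "The participant intercept and slope variances were fixed at 2.3 and 0.3, respectively". The error variance is 2.0 and the effect size 0.48.
- **Allocation** (Assignment of Interventions): "There will be no stratification".

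**The concern.** Because treatment is randomised, the true baseline means of the two groups are equal. An analysis that uses this fact, by conditioning on baseline or by fitting one common baseline mean, estimates the same treatment difference as the change-score comparison. Apart from the trivial cost of estimating one coefficient, it does so with no more variance. The gain is largest when baseline and end point are only moderately correlated, which is what the planning variances imply.

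Precision is scarce in this trial. The Objectives give a total of 66 (33 per group), Sample Size Determination gives 156, and 18 participants had completed by April 2025. At the smaller total, power for the assumed effect is about one half.

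**Working it through.** **Inputs.** Intercept variance 2.3, slope variance 0.3, error variance 2.0, effect size 0.48, 80% power, 5% type 1 error (2-sided), 10% attrition, all from Sample Size Determination except the 2-sided test, which is in the statistical methods. Assumed because not stated: zero intercept-slope covariance, and baseline at time 0 with end point at time 1.

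**Variances.**
- Var(baseline) = 2.3 + 2.0 = 4.3
- Var(end point) = 2.3 + 0.3 + 2.0 = 4.6
- Covariance = 2.3, so correlation = 2.3 / √(4.3 × 4.6) = 0.517
- Var(change) = 4.3 + 4.6 - 2 × 2.3 = 4.30

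**The plan's own figure.** Take the effect as 0.48 × √4.6 = 1.03. An unadjusted change-score test then needs n = 2 × (1.96 + 0.84)² × 4.30 / 1.03² ≈ 63.7 per group, and 63.7 / 0.9 = 70.8, against 71 stated. A slope test over times 0, 1, 2, with the effect scaled to the SD at time 2, gives 64.4 / 0.9 = 71.6. The assumptions are thus compatible with the stated 71, though this does not prove them.

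**Baseline-adjusted variance.**
- 4.6 - 2.3² / 4.3 = 3.37
- 3.37 / 4.30 = 0.784, so about 22% of the variance is removed
- 1 / 0.784 = 1.276, so the unadjusted test needs about 28% more patients

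**Does the mixed model already recover this?** No. In a three-visit generalised least squares fit with time as categories and group-specific baseline means, the end-point contrast has variance 8.60 for one patient per group, which is 2 × 4.30. With a common baseline mean it is 6.74 = 2 × 3.37. Having baseline among the responses does not help unless the groups share a baseline mean.

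**Linear group-by-time slope (times 0, 1, 2).** Unconstrained variance is 2 × (0.3 + 2.0/2) = 2.60. With a common baseline it is 2.096. The saving is 19%, or 24% more patients for the unconstrained test.

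**Sensitivity of the end-point saving.**

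| Assumption | Variance removed | Extra patients, unadjusted |
|---|---|---|
| Intercept-slope correlation -0.5 | 32% | 46% |
| Zero | 22% | 28% |
| Intercept-slope correlation +0.5 | 14% | 16% |
| Baseline-to-end-point correlation 0.73, equal variances | 13.5% | 16% |
| Baseline-to-end-point correlation 0.90, equal variances | 5% | 5% |

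The last two rows use the ratio (1 + ρ)/2: 0.865 and 0.95.

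**Power** = Φ(effect / √(2V/n) - 1.96), with V the relevant variance.

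| Effect | n per group | V = 4.30 | V = 3.37 |
|---|---|---|---|
| 0.48 × SD of end-point score (1.03) | 33 | 52% | 62% |
| 0.48 × SD of change (0.995) | 33 | 50% | 60% |
| 0.48 × SD of end-point score | 71 | 84% | 92% |
| 0.48 × SD of change | 71 | 82% | 90% |

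**Chance baseline imbalance.** A change score subtracts baseline with coefficient 1, whereas the implied regression coefficient is 2.3 / 4.3 = 0.53. At 33 per group, a baseline difference of one standard error is √(2 × 4.3 / 33) = 0.51. It shifts the change-score estimate by 0.51 × (1 - 0.53) = 0.24, about 23% of the assumed effect of 1.03.

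**The case against.** The strongest reply is that nothing here is an error. A comparison of change between randomised groups is unbiased and matches the stated outcome. It is made inside a longitudinal model with covariates, and the covariate list is open-ended, so a fuller analysis plan could add baseline. The validity part stands in full: this is a loss of efficiency, not a bias. The open list does not remove the point, because the article fixes the contrast itself, and that contrast uses each group's own baseline mean.

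The reply is also right about size. The correlation of 0.52 comes from planning variances, not from Executive Composite data, and the intercept-slope covariance and time coding are unstated. The test-retest values in Table 1 run from 0.73 to 0.98. They belong to other tests, but if the composite were as stable, the gain would be well below 22%. The calculation also leaves out the planned medication and mood covariates.

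Two further inferences are tempting but unsupported. One is that, without stratification, chance baseline imbalance goes uncorrected. Change scores in fact over-correct it, and the article does not say whether allocation is blocked. The other is that the change is entirely free. Human Subject Ethics Approval requires important modifications to go to the sponsor, IRB and FDA before implementation, with the registration updated, and a new primary analysis model could well fall under that.

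**Conclusion.** The point holds as a recommendation to improve efficiency. The end-point test is valid, but it forgoes precision that the collected baseline would give. On the planning variances the saving is about 22% of the variance (28% more patients for the unadjusted test). It is 14% to 32% over intercept-slope correlations of +0.5 to -0.5, and about 19% for the linear group-by-time slope. All of these rest on the stated variance components; the 22% and 19% also assume zero covariance, and the end-point figures place end point at time 1.

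A reader might take 22% and 28% as a fixed loss. The documents do not support that, because the composite's own baseline-to-end-point correlation is not given, and at 0.90 the saving falls to 5%. The power gain at 33 per group is about 10 percentage points under either scaling of the effect, but it depends on the same variances. The direction does not depend on them: in every scenario examined, baseline adjustment lowers the variance.

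**What to change.** For the primary outcome, specify a longitudinal mixed model with one common baseline mean and separate group effects at end point and follow-up. The primary test is the group effect at end point. Equivalently, model end point and follow-up as responses with baseline Executive Composite, by visit, as a covariate. Treat each secondary outcome in the same way with its own baseline. The treatment difference keeps its meaning as the between-group difference in change.

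The cost is small: revised wording and code, plus a prospective amendment and registry update made before unblinding, through whatever approvals the protocol's modification rule requires. Data collection runs to March 2027, so there is time. No extra visits, data or patients are needed.
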